#### Strategies to improve adherence to interventions {11c}

Low adherence can have a substantial effect on statistical power and biased estimates of an intervention’s effect. To improve adherence to intervention protocols, during the treatment phase, we will distribute medicines once a week to evaluate the participant’s drug consumption and monitor adherence in a timely manner. Face-to-face adherence-reminder sessions will take place during the medicine dispensing process. After treatment, the drug package will be returned to the researchers. Compliance will be self-reported by participants and will be assessed by investigators at each visit. Compliance is calculated using the following formula: compliance = (actual amount of internal use/total amount of internal use) × 100%. Poor compliance is predefined as compliance < 80%. After 28 days of treatment, participants with poor compliance will be removed from the per protocol set (PPS).

#### Relevant concomitant care permitted or prohibited during the trial {11d}

Concerning standardized treatment, during the run-in period and treatment period, aspirin, statin lipid-lowering drugs, angiotensin converting enzyme inhibitors (ACEIs), or angiotensin receptor blockers (ARBs) should be used. TCM formulations with a similar composition and efficacy to those of study drugs will not be allowed to be used. Researchers should record the concomitant medication accurately and maintain dose stability during the trial. The participants should be clinically stable for the last 1 month or receiving standardized treatment for ≥1 month with no modification of dosage or intravenous administration.

Concerning emergency care, in the event of an acute angina pectoris attack during treatment, participants should be treated with nitroglycerine first (one tablet at a time, by sublingual administration, which can be repeated every 5 min until the pain is relieved). If the pain persists after the total amount reaches 3 tablets in 15 min, medical attention should be sought immediately. The treatment status should be recorded. If the participant’s condition deteriorates during treatment and it is not advisable to continue the trial, the researcher should consider terminating the trial and switching to surgery or another type of clinical treatment, and the patients will be classified in the analysis as “treatment ineffective”.

#### Provisions for post-trial care {30}

If SAEs occur during the study period, the participants are also required to be followed up after the study period. Appropriate measures will be taken to fully protect the interests of participants, such as outpatient or inpatient care or referrals to other specialists.

### Outcomes {12}

#### Primary outcome

The primary outcome is the efficacy rate of stable angina symptom score classification [24]. The stable angina symptom score includes the attack frequency, duration, activity level of effort-induced angina pectoris, and pain degree. The indicators of the baseline period (0 weeks) and treatment period (28 days) will be compared.

#### Secondary outcomes

The secondary outcomes are the effect on ECG [25], change in Seattle Angina Questionnaire (SAQ) scores [26], and nitroglycerine consumption during the treatment period. Patients will be asked to complete an SAQ (at the baseline period and at the end of the 4-week treatment), which is a 19-item self-administered questionnaire, to measure five dimensions of health. Researchers will record nitroglycerine consumption during the treatment period and compare this among groups.

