***Secondary outcomes***				
ECG parameters	Classification of 12-lead ECG improvement [23]	Difference between two groups	Proportion	Baseline, 28 days after treatment
SAQ scores	SAQ [24]	Difference in the change between groups	Mean/ median	Baseline, 28 days after treatment
Nitroglycerin consumption	Count	Compare the difference between groups	Median	Baseline, 28 days after treatment

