**Efficacy indicators**			
Stable angina symptom score		×	×
Electrocardiogram		×	×
Seattle Angina Questionnaire		×	×
Nitroglycerin consumption	×	×	×

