## Statistical methods

### Statistical methods for primary and secondary outcomes {20a}

The statistical analysis plan will be specified before data analysis. Statistical Analysis System v9.4 (or a higher version) will be used for statistical analysis. Professional statisticians who are independent of all other processes in our study will carry out the analyses.

For continuous variables, we will calculate the mean, standard deviation, median, minimum, maximum, and interquartile range. For categorical variables, we will report various frequencies or percentages. The chi-square test or Fisher’s exact test will be used for categorical variables. For variables with a normal distribution, intergroup comparisons will be analysed with one-way ANOVA, whereas pairwise comparisons before and after treatment will be performed with Student’s *t* test. For data that do not have a normal distribution, intragroup or intergroup differences before and after treatment will be analysed by the Wilcoxon rank-sum test. The proportion of patients with AEs will be compared using the chi-square test or Fisher’s exact test.

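### Nitroglycerine use is recorded before and during treatment, but no named analysis adjusts for the patient's own prior use: a loss of precision, not of validity

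*Protocol article*

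**What the plan says.** Five places in the protocol article bear on this outcome.

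- **Outcomes {12}, Secondary outcomes.** The outcome is use in the treatment period: "Researchers will record nitroglycerine consumption during the treatment period and compare this among groups".
- **Table 3.** The row reads "Nitroglycerin consumption Count Compare the difference between groups Median Baseline, 28 days after treatment". The metric is a between-group difference summarised by a median, with baseline listed as a time-point. The neighbouring SAQ row has a different metric: "Difference in the change between groups".
- **Table 4.** "Nitroglycerin consumption" is marked in all three columns: run-in, baseline and intervention.
- **Statistical methods {20a}.** For normally distributed variables, "intergroup comparisons will be analysed with one-way ANOVA". Otherwise, "intragroup or intergroup differences before and after treatment will be analysed by the Wilcoxon rank-sum test". Neither test carries a covariate.
- **Additional analyses {20b}.** An analysis of covariance is planned with sex, site, complications and other medication. Prior nitroglycerine use is not in the list.

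**The concern.** How many tablets a patient took before randomisation is the most direct available predictor of how many he or she takes afterwards. Angina grades I to III are all eligible, so rescue need will probably differ widely between patients. Background treatment is meant to be stable before and during the trial, so prior use is measured under similar conditions to later use. A test that ignores prior use leaves all of that between-patient spread in the error term, in arms of only 64, 32 and 32.

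The outcome window, the metric, the type of test and the covariate list are all written down. Taken together they leave out the one covariate tied directly to this outcome, although the trial already collects it. What is at stake is the precision of a supporting secondary outcome. A second problem is that the article can be read as prescribing two different analyses: treatment-period level, or change from baseline.

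**Working it through.** **What the article quantifies.** Sample size {14} concerns only the symptom-score efficacy rate. Its figures reproduce: response rates of 50%, 70% and 85% with equal weights give W = 0.30821; a 2-df chi-square test then needs N = 102 (power 0.8024); and 102/0.8 = 127.5, rounded up to 128. For nitroglycerine use the article gives no effect, variance, correlation or power, so there is no figure of its own to reproduce. Everything below rests on assumed values.

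**Formula.** For one pairwise comparison, let rho be the correlation between pre-treatment and treatment-period use. Relative to treatment-period use alone (variance 1, equal variances before and during treatment):

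- covariate adjustment leaves variance 1 − rho²;
- a change score has variance 2(1 − rho).

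The new power is Φ[(1.960 + z_base)/√v − 1.960], where v is the relative variance and z_base is the normal quantile of the starting power.

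**Covariate adjustment.** For 80% starting power, 1.960 + 0.842 = 2.802. At rho = 0.5, √0.75 = 0.866, 2.802/0.866 = 3.235, 3.235 − 1.960 = 1.275, and Φ = 89.9%. The same steps give:

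| Assumed rho | 1 − rho² | From 80% | From 60% |
|---|---|---|---|
| 0.2 | 0.96 | 81.6% | 61.8% |
| 0.3 | 0.91 | 83.6% | 64.1% |
| 0.5 | 0.75 | 89.9% | 72.4% |
| 0.7 | 0.51 | 97.5% | 87.3% |

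**Change score, from 80%.** At rho 0.3, v = 1.4 and power falls to 65.8%. At 0.5, v = 1.0 and power stays at 80.0%. At 0.7, v = 0.6 and power is 95.1%. Because 1 − rho² = (1 − rho)(1 + rho) and 1 + rho ≤ 2, adjustment is never less efficient than the change score. It is also never less efficient than treatment-period use alone.

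**Skewed counts.** Tablet counts are not normal, so overdispersed counts were simulated for 51 v 26 patients with an assumed rate ratio of 0.6, in 16 settings of 800 runs each. Rank correlations ran from about 0.25 to 0.73. Rank ANCOVA had the highest power in all 16 settings. Its gain over the rank-sum test on treatment-period use ran from about 0 to 24 points. It was usually smaller with one pre-treatment week than with three. The rank-sum test on change did worse than the rank-sum test on treatment-period use in 11 of the 16.

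**Validity.** In a separate simulation with no treatment effect (4,000 trials per scenario), the rank-sum test rejected in 5.1% to 5.3% and rank ANCOVA in 4.8% to 5.0%. Both hold the nominal 5%.

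**The texts side by side.** The Secondary outcomes text speaks of treatment-period use only. Table 3 lists baseline as well, yet gives the metric as "Compare the difference between groups", not the change metric used for SAQ. The Wilcoxon sentence can mean a test on before-after differences. These do not describe a single analysis.

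**The case against.** The strongest reply is that the article does not clearly discard baseline use. Table 3 names baseline as a time-point, and the Wilcoxon sentence can be read as a test on change, in which case prior use enters through subtraction. That stands as a reading, so it would be wrong to say that the plan plainly throws the pre-treatment data away. It does not remove the point. The reading conflicts with the Secondary outcomes text, and a change score gains nothing at rho = 0.5 and loses below it.

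A second reply is that the analysis plan is still to come, and covariates for a secondary outcome often belong there. That would settle the matter if the article were silent, but it gives a covariate list and a family of tests.

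Two stronger readings are tempting and not supported. A reader might infer a loss of about 10 points of power. That figure needs both an assumed correlation of 0.5 and an assumed starting power of 80%; the article states neither for this outcome and did not power it. A reader might also infer that a chance imbalance in prior use would be mistaken for a drug effect, so that the comparison is biased. Under randomisation the unadjusted test already allows for such imbalance and keeps its 5% size. Nor does the article show that tablet use is mainly a stable patient characteristic: even rho = 0.5 would explain only 0.25 of the variance.

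**Conclusion.** The point holds as one of efficiency and consistency. The named tests are valid, but none uses prior nitroglycerine use as a covariate, and the outcome text, Table 3 and the methods sections do not agree on whether level or change is compared. The likely benefit of adjustment is modest to substantial: from 80% power, between 3.6 and 17.5 points for rho from 0.3 to 0.7; from 60%, between 4.1 and 27.3 points. It could be close to nil if prior use is sparse, covers one week only, or is weakly related to later use. These figures assume a pairwise comparison, a linear relation and a correlation that the article does not supply. Since the outcome is secondary and unpowered, the change is worthwhile but does not affect the soundness of the trial.

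**What to change.** Reconcile the Secondary outcomes text, Table 3, the statistical methods {20a} and the additional analyses {20b} so that they describe one analysis: treatment-period nitroglycerine use compared between arms, with the patient's pre-treatment use as a covariate and site, the randomisation stratum, as a factor. Prespecify one method. Rank ANCOVA suits skewed counts: ranks of treatment-period use regressed on arm, ranks of prior use, and site. Keep medians as description.

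Express prior use as a weekly rate, because the periods differ in length, and count it over non-overlapping days. Trial design {8} describes two weeks of run-in followed by one week of baseline, whereas the Table 4 column headings, (−14 ± 1) day and (−7~0) days, do not show whether the windows are separate. Adding them without settling this could count days twice.

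The cost is a few lines of wording and one decision about the pre-treatment window. The data are already scheduled, and the article reports that no analysis has been done and that the analysis plan will be specified before data analysis.

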#### Safety outcomes

Safety evaluations will include vital signs (heart rate, respiration, body temperature, blood pressure); clinical laboratory tests (routine blood test, routine urinalysis, serum biochemistry, blood coagulation index, fasting blood glucose), AEs, and SAEs.

The five elements of the primary outcome, secondary outcomes, and safety outcomes are shown in Table 3.

**Table 3 Tab3:** The five elements of the outcomes

Domain	Specific measurement	Specific metric	Method of aggregation	Time-points
***Primary outcome***				
Stable angina symptom score	Symptom score standard classification [22]	Difference between two groups	Proportion	Baseline, 28 days after treatment
***Secondary outcomes***				
ECG parameters	Classification of 12-lead ECG improvement [23]	Difference between two groups	Proportion	Baseline, 28 days after treatment
SAQ scores	SAQ [24]	Difference in the change between groups	Mean/ median	Baseline, 28 days after treatment
Nitroglycerin consumption	Count	Compare the difference between groups	Median	Baseline, 28 days after treatment
***Safety outcomes***				
Vital signs	Heart rate, respiration, body temperature, blood pressure	Compare the difference between groups	Mean/ median	Run-in period, baseline, 28 days after treatment
Clinical laboratory tests	Routine blood test, routine urinalysis, serum biochemistry, blood coagulation index, and fasting blood glucose	Compare the difference between groups	Mean/ median	Baseline, 28 days after treatment
AEs, SAEs	Common Terminology Criteria for AEs version 4.03.	Compare the difference between groups	Proportion	Baseline, 28 days after treatment

*ECG* electrocardiogram, *SAQ* Seattle Angina Questionnaire

### Participant timeline {13}

The measurement items and timeline for data collection in this study are displayed in Table 4.

**Table 4 Tab4:** Measurement items and time points for data collection

Item	Run-in period (−14 ± 1) day	Baseline period (−7~0) days	Intervention period (28 ± 4) days
**Basic information**			
Informed consent	×		
Inclusion/exclusion criteria		×	
Demographic data	×		
Randomization		×	
Record medical history and allergy history	×		
Record complication and symptom	×		
Record concomitant medication	×		
Access to the “Doctor Tao” platform	×		
Urine pregnancy test	×		
**Safety assessment**			
Vital signs and physical examination	×	×	×
Blood and urine routine examination		×	×
Liver function (ALT, AST, AP, TBIL, γ-GT)		×	×
Kidney function (SCr, BUN)		×	×
Coagulation function (PT, APTT, TT, FIB, INR)		×	×
Fasting blood glucose		×	×
**Efficacy indicators**			
Stable angina symptom score		×	×
Electrocardiogram		×	×
Seattle Angina Questionnaire		×	×
Nitroglycerin consumption	×	×	×
**Other works**			
Drug distribution	×	×	
Drug recycling		×	×
Record adverse events and combined medication		×	×
Compliance judgement		×	×

*ALT* alanine aminotransferase, *AST* aspartate aminotransferase, *AP* alkaline phosphatase, *TBIL* total bilirubin, *γ-GT* γ-glutamyl transpeptidase, *SCr* serumcreatinine, *BUN* blood urea nitrogen, *PT* prothrombin time, *APTT* activated partial thrombolastin time, *TT* thrombin time, *FIB* fibrinogen, *INR* international normalized ratio

### Sample size {14}

The sample size is calculated using PASS 15 software (NCSS, Kaysville, UT) and driven by the efficacy rate of stable angina symptom score improvement. According to the referenced literature [27, 28], the efficacy rate in relieving stable angina symptoms of NXT is expected to be 85%, 70% for BYHW, and 50% for placebo.

The PASS parameters are as follows: “Proportions>Contingency Table (Chi-Square Tests)>Chi-Square Tests”, “Chi-Square Effect Size Estimator> Contingency Table”. Input the percentage values: placebo = 50%, BYHW = 70%, NXT = “85%”, copy effect size = “0.308210”. Design solve for “sample size”, DF = 2, Power = 0.8, Alpha = 0.05, input effect size = “0.308210”. Then we can get numeric results: *N* = 102, Chi-square = 9.6893, Alpha = 0.05000, Beta = 0.19763. Considering a drop rate of 20%, the dropout-inflated sample size = 128, and expected number of dropouts = 26. According to the ratio of 2:1:1, there will be 64 cases in intervention group 1, 32 cases each in the intervention group 2 and control group. Since this study intends to further compare the NXT and BYHW groups, according to NXT = 85%, BYHW = 70%, W = 0.3082, DF = 1, and the sample size of NXT and BYHW calculated in the previous step, we can reach a power of 0.85540.

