### Objectives {7}

The objectives of this study were (i) to evaluate the efficacy of NXT and BYHW in the treatment of SAP and (ii) to test whether NXT is more advantageous than BYHW for treating SAP.

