Modern clinical studies have shown that BYHW can significantly improve the effectiveness of angina pectoris; reduce the attack duration, degree of pain, and nitroglycerine consumption; and improve the blood lipid index [28]. NXT is a next-generation innovation of the basic formula of BYHW. Li et al. systematically evaluated the efficacy and safety of NXT in the treatment of SAP, which included 44 studies and 5130 patients. The results showed that NXT can significantly improve ECG efficacy, relieve angina symptoms, and improve clinical efficacy [30]. In addition, there is evidence that both NXT and BYHW can protect vascular endothelial function, delay the process of atherosclerosis, improve haemorheological indicators, reduce blood lipids, have anti-inflammatory and antithrombotic effects, and exert obvious protective effects against myocardial ischaemia-reperfusion injury [14–17]. Since the two Chinese patent medicines have similar indications, mechanisms, and clinical efficacy for SAP, we designed a protocol to observe the efficacy and safety of NXT and BYHW in the treatment of SAP.

However, this study has limitations. First, AEs will only be recorded and processed during the 4-week intervention period, which is relatively short, but these short-term results could encourage further prospective studies with different treatment regimens and longer follow-up periods. Second, due to the short intervention period, this study lacks long-term observations of mortality and cardiovascular events. A large-scale and long-term future study that assesses mortality and cardiovascular events as the primary endpoint is expected.

In conclusion, under rigorous design and strict quality control, we expect that the results of this study will provide valuable evidence to determine whether the effect of NXT is superior to that of BYHW for improving the symptoms of patients with SAP.

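### The 85.5% power stated for NXT versus BYHW reuses the three-group effect size; at the plan's own rates it is about 41% with all 96 patients, or 34% after the planned dropout

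*Protocol article*

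**What the plan says.** Sample size {14} of the protocol article sets the planning rates: "the efficacy rate in relieving stable angina symptoms of NXT is expected to be 85%, 70% for BYHW, and 50% for placebo". It builds the effect size from all three groups: "Input the percentage values: placebo = 50%, BYHW = 70%, NXT = “85%”, copy effect size = “0.308210". The overall test then uses "DF = 2, Power = 0.8, Alpha = 0.05, input effect size = “0.308210", which gives N = 102. Allowing for 20% dropout, this becomes 128 patients, split 64, 32 and 32.

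The closing sentence turns to the pairwise question. It uses "NXT = 85%, BYHW = 70%, W = 0.3082, DF = 1, and the sample size of NXT and BYHW" from the preceding step and concludes that "we can reach a power of 0.85540".

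That comparison is objective (ii) in Objectives {7}: "to test whether NXT is more advantageous than BYHW for treating SAP". It is repeated in the explanation of comparators {6b}. The Discussion expects the results to "provide valuable evidence to determine whether the effect of NXT is superior to that of BYHW".

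**The concern.** The closing sentence changes the degrees of freedom from 2 to 1 but leaves W as it was. W summarises how far a given set of proportions departs from their common mean. Removing the 50% placebo group changes both that mean and the spread, so W for NXT against BYHW must be recalculated from 85% and 70% alone. The sentence lists those two rates next to a W that they do not produce.

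The sample size in this step also appears to be the number randomised, although the same paragraph expects to lose 20%.

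No other power figure is given for objective (ii), and this one tells the reader that a size chosen for the three-group test also serves the head-to-head question. If it is wrong, the chance of missing the assumed difference is far above the one in seven implied, and a non-significant result could be mistaken for evidence that the two products perform alike.

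**Working it through.** **Inputs**, all from Sample size {14}: response rates 85% (NXT), 70% (BYHW) and 50% (placebo); alpha 0.05; arms of 64, 32 and 32; dropout 20%; W = 0.308210; stated pairwise power 0.85540.

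**Formulas.** With group weights w and weighted mean rate p̄:
- W² = Σ w(p − p̄)² / [p̄(1 − p̄)]
- power = P(χ² with noncentrality N·W² exceeds the critical value); the critical value is 3.841 for 1 df at alpha 0.05.

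**1. The plan's three-group figures.** Equal weights give p̄ = (0.50 + 0.70 + 0.85)/3 = 0.6833. The squared deviations are 0.03361, 0.00028 and 0.02778, with mean 0.02056. Then W² = 0.02056/0.21639 = 0.09499 and W = 0.30821, as printed. With N = 102 and 2 df, the noncentrality is 9.6893 and power is 0.8024, also as printed (beta 0.19763). Placebo supplies 0.03361/0.06167, about 55%, of this sum of squares.

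**2. The plan's pairwise figure.** W = 0.30821, N = 64 + 32 = 96 and 1 df give noncentrality 96 × 0.09499 = 9.12 and power 0.85540, an exact match. So the three-group W was used, with the dropout-inflated arm sizes.

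**3. The correct W.** At 2:1, p̄ = (2 × 0.85 + 0.70)/3 = 0.80. W² = [(2/3)(0.05)² + (1/3)(0.10)²]/(0.80 × 0.20) = 0.005/0.16 = 0.03125, so W = 0.1768. Equal weights would give 0.1796. To obtain W = 0.3082 at 2:1 with NXT at 85%, BYHW would have to be about 57%, not 70%.

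**4. The correct power.** Evaluable patients after 20% dropout: 96 × 0.8 = 76.8, taken as 77 (about 51 and 26).

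| Method, 85% v 70% | 64 v 32 (N = 96) | 51 v 26 (N = 77) |
|---|---|---|
| Noncentral χ², W = 0.1768 | 0.410 (noncentrality 3.00) | 0.342 (noncentrality 2.41) |
| Noncentral χ², W = 0.1796 | 0.421 | 0.351 |
| Two-proportion formula, pooled null variance | 0.416 | 0.352 |
| Exact enumeration, Pearson test | 0.424 | 0.347 |
| Exact enumeration, Fisher's exact test | 0.359 | 0.300 |
| Two-proportion formula, one-sided 5% | 0.533 | 0.466 |

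**5. Separating the two faults.** Keeping the wrong W and correcting only N to 77 gives 0.772. Correcting only W at N = 96 gives 0.410. The reused W accounts for most of the discrepancy.

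**6. What the design can show.** With 51 v 26 evaluable and BYHW at 70%, 80% power needs NXT at about 94%. The expected 95% confidence interval half-width for the difference is:
- 64 v 32: 1.96 × √(0.85 × 0.15/64 + 0.70 × 0.30/32) = 1.96 × 0.0925 = 0.18
- 51 v 26: 1.96 × √(0.85 × 0.15/51 + 0.70 × 0.30/26) = 1.96 × 0.1028 = 0.20

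Both exceed the assumed difference of 15 points. For context only, 80% power for 85% v 70% at 2:1 needs about 252 evaluable patients in these two arms.

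**The case against.** The strongest reply concerns dropout. Section {20c} defines the full analysis set as all randomised patients with at least one dose and carries the last observation forward. Section {11b} keeps existing data after withdrawal, and section {11d} counts patients who deteriorate and stop as ineffective. On that reading 96 is close to the planned denominator and 77 is nearer the per-protocol set. This has force, and it is why 41% is the headline and 34% is the plan's own dropout scenario. It does not rescue the stated figure, because 41% already assumes that nobody is lost.

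It can also be said that 0.85540 did not set the sample size. That is true: the three-group calculation reproduces. Its W assumes equal groups, but 2:1:1 weights give W = 0.322 and power of about 84% at N = 102, so the unequal allocation does no harm to that step.

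Finally, the article nowhere says that a null result would show equivalence, and how the comparison is reported could be left to the statistical analysis plan. That is fair as to the reporting text, which guards against a misreading and is not itself arithmetic. It does not excuse a wrong number printed in the protocol, which a later analysis plan would not correct.

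**Conclusion.** The stated power is wrong and must be corrected. The true value at the plan's own rates is about 41% if all 96 patients are analysed and about 34% if 20% are lost from each arm, against a printed 85.5%. A real 15-point advantage for NXT would be missed in 59% to 66% of trials, where the text implies 14.5%.

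The result rests on the plan's 85% and 70%, its 64 and 32 patients, and a two-sided test at 0.05. The lower figure also assumes equal dropout in the two arms. None of the standard variants tried comes near 0.855; the most favourable, a one-sided 5% test with no dropout, reaches about 53%. The error is confined to the NXT versus BYHW statement: N = 102 and the inflated 128 stand.

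**What to change.** Replace the last sentence of Sample size {14} with text to this effect:

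*For NXT 85% versus BYHW 70% at 2:1 allocation and two-sided alpha 0.05, W = 0.177. Power is about 41% with 96 patients and about 34% with 77 evaluable patients after 20% dropout. The comparison will be reported as a risk difference with its 95% confidence interval, whose expected half-width is about 18 to 20 percentage points. A non-significant result will not be interpreted as similar efficacy.*

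Delete 0.85540. The corrected W and power are the essential part; the reporting sentences tell the reader what the comparison can support. The cost is one rewritten statement and a much less favourable figure. Enrolment, allocation and conduct do not change. Trial status describes recruitment as in progress with no analysis carried out, so on that status the correction can be made before results are known.

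### The stated 0.85540 power for NXT versus BYHW uses the three-group effect size and the dropout-inflated N; under the plan's own rates the power is about 35–42%

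*Protocol article*

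**What the plan says.** The Sample size section of the protocol article (item 14) starts from assumed efficacy rates: "the efficacy rate in relieving stable angina symptoms of NXT is expected to be 85%, 70% for BYHW, and 50% for placebo". It enters these in a three-row contingency table, obtains W = 0.308210, and sizes the overall test with "DF = 2, Power = 0.8, Alpha = 0.05, input effect size = “0.308210". The output is N = 102 with "Chi-square = 9.6893, Alpha = 0.05000, Beta = 0.19763". Inflation for 20% dropout gives 128, split 64/32/32.

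The same paragraph then turns to NXT against BYHW. It restates the rates 85% and 70%, keeps W = 0.3082, and concludes: "DF = 1, and the sample size of NXT and BYHW calculated in the previous step, we can reach a power of 0.85540".

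This comparison is not incidental. Objective (ii) is "to test whether NXT is more advantageous than BYHW for treating SAP", and the Discussion closes by promising "valuable evidence to determine whether the effect of NXT is superior to that of BYHW".

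**The concern.** W depends on the table it is computed from. The three-group value is driven largely by the distance between the 50% placebo rate and the rest, and the placebo arm takes no part in NXT versus BYHW. Carrying that W into a one-degree-of-freedom test of 85% against 70% credits the comparison with an effect that the assumed rates do not contain. Using 96 patients also sets aside the 20% loss that the same paragraph has just allowed for.

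Readers are told that this comparison has 86% power. If the true figure is less than half of that, a non-significant result says little about whether NXT is better, but beside a claim of 86% power it could easily be taken as evidence of no difference.

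**Working it through.** **Inputs (all from Sample size, item 14).** Rates: NXT 0.85, BYHW 0.70, placebo 0.50. Alpha 0.05, chi-square test. Arms 64/32/32. Dropout 20%, so 64 × 0.8 = 51.2, 32 × 0.8 = 25.6 and 96 × 0.8 = 76.8, taken as about 51 + 26 = 77 evaluable.

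**Formulas.** With allocation fractions aᵢ and weighted mean rate p̄:

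- W² = Σ aᵢ(pᵢ − p̄)² / [p̄(1 − p̄)]
- λ = N·W²
- Power = P(non-central χ² with df and λ exceeds the central 5% critical value)

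**Step 1: reproduce the overall test.** Equal arms: p̄ = (0.50 + 0.70 + 0.85)/3 = 0.6833. Squared deviations 0.03361, 0.00028 and 0.02778 have mean 0.020556. W² = 0.020556/0.21639 = 0.09499, so W = 0.30821. At N = 102, λ = 9.6893 and power with df = 2 is 0.8024. Both agree with the plan.

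**Step 2: reproduce the pairwise figure.** W = 0.30821, df = 1:

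| N | Power |
|---|---|
| 77 (after dropout) | 0.772 |
| **96 (64 + 32)** | **0.85540** |
| 102 | 0.876 |

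The stated value therefore comes from the three-group W and the dropout-inflated 96.

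**Step 3: the correct two-group effect size.** At 2:1, p̄ = (2 × 0.85 + 0.70)/3 = 0.80. W² = (2/3)(1/3)(0.15)²/(0.80 × 0.20) = 0.005/0.16 = 0.03125, so W = 0.1768. At 1:1, W = 0.1796.

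**Step 4: the correct power, two-sided 0.05.**

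| Method | 64/32 | about 51/26 |
|---|---|---|
| Non-central χ², W = 0.1768 | 0.410 (λ = 3.00) | 0.342 (λ = 2.41) |
| Two-proportion normal formula | 0.416 | 0.352 |
| Exact enumeration of the χ² test | 0.424 | 0.347 |
| Fisher's exact test (also allowed by the plan) | 0.359 | 0.300 |

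A one-sided test at 0.05 would give 0.53 and about 0.46–0.47, still far below 0.855.

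**Step 5: what 0.855 would require.** The plan's λ is 96 × 0.09499 = 9.12. With W² = 0.03125, N = 9.12/0.03125 = 291.8, or about 292 evaluable patients in the two arms. Alternatively, at 64/32 an NXT rate of about 93% against 70% gives W = 0.306 and power 0.85. The plan assumes neither.

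**Step 6: expected precision.** At 64/32 the standard error of the difference is √(0.85 × 0.15/64 + 0.70 × 0.30/32) = 0.0925, so the 95% half-width is about 18 points around an assumed difference of 15. At 51/26 it is about 20 points.

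**Step 7: the omnibus W.** The value 0.308210 is for equal arms, but the trial allocates 2:1:1. Then p̄ = 0.725, W² = 0.020625/0.199375 = 0.10345 and W = 0.3216. N = 102 gives power 0.837, and N = 94 would suffice for 80%. This slip is conservative.

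**Step 8: the other pairs (exact χ² power).** NXT versus placebo: 0.954 at 64/32 and 0.908 at 51/26. BYHW versus placebo: 0.392 at 32/32 and 0.321 at 26/26.

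**The case against.** **The trial is sized on the three-group test, and NXT versus BYHW is a further comparison.** This is true, and the 102 and 128 stand. But the protocol chose to print a pairwise power with its inputs, and the comparison is a stated objective and the subject of the conclusion. The error is a wrong number, not a missing detail that an analysis plan could supply.

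**N = 96 may be legitimate.** The full analysis set takes every randomised patient with at least one dose, and missing values are carried forward (item 20c). Close to 96 patients may therefore be analysed, and the 34–35% figure fits a complete-case or per-protocol analysis better. This stands in part: the wrong W does most of the damage, since keeping W = 0.3082 and lowering N to 77 would still give 0.77. But accepting 96 raises the correct power only to about 42%, and that assumes the full 85% and 70% rates among everyone analysed. Tables 3 and 4 place the symptom score only at baseline and day 28, so a dropout carried forward would count as unimproved. If, as an illustration, 20% of each arm were lost this way, the rates become 68% and 56%, W² = (2/9)(0.12)²/(0.64 × 0.36) = 0.0139, λ = 1.33 and power is about 21%.

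**The omnibus slip is harmless.** Agreed: the overall test is slightly better powered than stated. It belongs in the correction only because the same paragraph is being rewritten.

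**Low power does not forbid a pre-stated test.** Also fair. The test may stay, provided its power is stated honestly and the interval is reported.

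**Conclusion.** The stated power is wrong as written. Under the plan's own rates of 85% and 70%, with a two-sided 5% chi-square test and no multiplicity adjustment, NXT versus BYHW has about 41–42% power with all 64 + 32 analysed and about 34–35% after the assumed 20% dropout, against a stated 0.85540. Adjusting for several pairwise comparisons would lower it further. The result does not depend on the cited literature, because the printed rates and the printed W do not belong together. The omnibus sample size is unaffected, and its mis-specified W errs on the safe side. The pairwise figure must be corrected because a stated objective and the paper's conclusion rely on that comparison.

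**What to change.** In Sample size (item 14):

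- Replace 0.85540 with the power for W = 0.177: about 35% at the 77 patients expected to be evaluable, and 42% at most with no dropout.
- State that NXT versus BYHW will be reported as a difference in efficacy rates with a 95% confidence interval, and that the trial is not powered to show superiority.
- Give the other pairwise powers beside it: NXT versus placebo about 91–95%, BYHW versus placebo about 32–39%.
- Restate the overall test with the 2:1:1 effect size (W = 0.3216, power 83.7% at N = 102).

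In the Discussion, reword the conclusion so that it promises an estimate of the difference between NXT and BYHW, not a determination of superiority.

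The cost is one rewritten paragraph, one reworded sentence and a less favourable published power. Enrolment does not change. Trial status reports that recruitment is in progress and no analysis has been done, so the correction can precede any results.
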